#### Planned methods for analysis

Confirmatory analysis follows the intention to treat principle and will be based on the full analysis set. Time to event endpoints will be analyzed by Cox regression with arm as fixed effects, stratification criteria as fixed and center as random effect. The occurrence of safety endpoints (AE by Preferred Term/occurrences of toxicities of grades ≥3) will be compared by chi-square tests. Odds ratios with 95% confidence intervals will be provided. Serious adverse events will be reported descriptively (including a clinical causality assessment) by System Organ Class and Preferred Term according to MedDRA. In case of relevant frequencies of SAE and classified serious adverse reactions (by Preferred Term) exact Fisher test will be applied on SAE/SAR occurrences. No confirmatory subgroup analyses are planned. PD-L1 status will be analyzed in exploratory analyses. Safety issues will be carefully monitored. Regular safety analyses will be performed and presented to the Data-Monitoring Committee (DMC). Statistical monitoring will focus on data quality assurance. All analyses will be pre-specified in a detailed statistical analysis plan, which will be finalized before data base closure. The trial will be reported according to CONSORT criteria.

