#### Chemotherapy

The q1w and q3w schedule will be allowed in the ADRISK and may be applied according to the respective standard of the center. The dosing and timing of chemotherapy to be used in this trial is outlined in **Table 2**. These options were chosen since the q3w schedule is not very common in Germany. However, the balancing of the cisplatin/RT doses will be reviewed permanently to rule out bias between the arms and the cisplatin schedule is used as a stratification criterion. A minimum of 200 mg/m^2^ cisplatin should be aimed at in all patients. An intravenous infusion (volume replacement) will be given as supportive therapy. All patients receive adequate antiemetic prophylaxis. The choice between q1w and q3w is left to the appraisal of the radiation oncologist, considering age, weight loss before radiation, creatinine clearance and performance status. In practice, various radiotherapists systematically use q1w cisplatin, and others use q3w cisplatin. In case of poor radiochemotherapy tolerability, the patients have to be hospitalized or receive a nasogastric intubation.

**Table 2 T2:** Cisplatin treatment.

Drug	Dose/Body Surface Area	Frequency Dose/Body Surface Area	Route of Administration	Regimen/Treatment Period
Cisplatin	300 mg/m^2^	q3w 100 mg/m^2^	inravenous infusion	days 1, 22, and 43
Cisplatin	280 mg/m^2^	q1w 40 mg/m^2^	intravenous infusion	days 1, 8, 15, 22, 29, 36, 43 1-7th week

Patients must meet the following criteria before each new cycle:

• No hematotoxicity of grade ≥2 (i.e. neutrophils >1500/μL, platelets >100.000/μL, hemoglobin ≥9 g/dl, if required after transfusion)• Recovery from any treatment-related grade 3/4 non-hematological toxicity (except alopecia) to baseline or ≤grade 1• No ongoing requirement for anti-diarrheic treatment• Bilirubin ≤3.0 x ULN• Transaminases ≤2.5 x ULN• No peripheral neurotoxicity of grade 3• Creatinine clearance ≥60 mL/min• No treatment delay of more than 3 weeks

Patients not meeting the above criteria on the date scheduled for the new cycle must suspend treatment with the anticancer drugs until they meet the above criteria. In the case of a cisplatin intolerance during RCT, it may be possible to switch to carboplatin. The administration of mitomycin is not permitted.

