### Randomization process

Randomization of patients between experimental and control arm is performed centrally *via* a secure web-based tool using a modified minimization procedure with stochastic component according to Pocock (14) in a 1:1 proportion. Stratification is performed using the tumor localizations: 1) oral cavity, 2) oropharynx, 3) larynx, or 4) hypopharynx. For patient with oropharyngeal carcinoma, the p16-marker is generally determined in routine procedures and will be used as sub-classifier 2+) and 2-) so that 5 strata will be used in total. Furthermore, a stratification according to the q3w vs. q1w schedule of chemotherapy will be applied. Randomization will be balanced according to trial site as well. The result of the successful randomization is immediately available *via* the randomization tool and is forwarded automatically to the investigator and the Clinical Trial Center Leipzig.

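### Grade ≥3 toxicity is compared by unstratified chi-square tests although randomization is balanced on cisplatin schedule: a small possible loss of power, cheaply avoided

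*Protocol article*

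**What the plan says.** Under Planned methods for analysis, the protocol article says that adverse events by Preferred Term and toxicities of grade ≥3 "will be compared by chi-square tests", and adds: "Odds ratios with 95% confidence intervals will be provided". No strata or covariates are named for either. The same paragraph gives the Cox model for time-to-event endpoints "stratification criteria as fixed and center as random effect".

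Under Randomization process, allocation is by minimization with a stochastic component. It balances on tumor localization (with p16 status in the oropharynx) and on trial site, and "a stratification according to the q3w vs. q1w schedule of chemotherapy will be applied".

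Under Chemotherapy, the radiation oncologist chooses between the weekly and three-weekly schedule, "considering age, weight loss before radiation, creatinine clearance and performance status". Table 2 gives 100 mg/m² on three days (300 mg/m² in total) or 40 mg/m² on seven days (280 mg/m² in total).

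Under Analysis population, safety patients are grouped by whether they received any pembrolizumab, not by allocation. Footnote 4 of Table 4 collects adverse events until 90 days after the end of treatment in the experimental arm (or until a new anti-cancer treatment), but only until the month 3 visit in the control arm.

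**The concern.** The plan adjusts its efficacy analysis for the design factors and, as written, leaves them out of the toxicity comparison. Cisplatin schedule is a plausible predictor of toxicity on the article's own account: the dose per administration differs, and patient condition guides the choice.

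When a predictor of the outcome is balanced by design and then ignored, the variance used by the unstratified test includes a between-stratum part that balancing has removed from the arm comparison. The test then rejects less often than its nominal level and has less power than the data allow. Safety in terms of toxicity is a stated secondary goal, so some sensitivity could be given up there for no return.

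**Working it through.** The article gives no figure for the safety comparison, so there is none to reproduce.

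**Inputs from the article.** 240 patients randomized 1:1, so 120 per arm; schedule as a balancing factor; chi-square test; odds ratio as effect measure.

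**Assumptions, not in the article.** Half the patients on each schedule (60 per arm and schedule); exact balance; two-sided 5% test; within-schedule odds ratio of 2 for pembrolizumab; the control rates shown below.

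**Formulas.** Let p₁ and p₂ be the control rates in the two schedules and p̄ their mean.
- Variance ratio: R = [p₁(1−p₁) + p₂(1−p₂)] / [2 p̄(1−p̄)].
- True size of the nominal 5% unstratified test: about 2[1 − Φ(1.96/√R)].
- Rate under an odds ratio of 2: 2p/(1 + p). Average this over the two schedules, then take the ratio of the odds to get the marginal odds ratio.

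**Worked case, 40%/80%** (schedule odds ratio (0.8/0.2)/(0.4/0.6) = 6). R = (0.24 + 0.16)/(2 × 0.24) = 0.833. Size = 2[1 − Φ(2.147)] = 3.2%. Experimental rates are 57.1% and 88.9%, mean 73.0%. Marginal odds ratio = (0.730/0.270)/(0.6/0.4) = 1.80.

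**All cases.** Power is from simulation of the chi-square test against the Cochran-Mantel-Haenszel (CMH) test by schedule (400,000 runs).

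| Control rates | Schedule OR | R | Size, formula | Size, simulated | Marginal OR | Power, chi-square | Power, CMH |
|---|---|---|---|---|---|---|---|
| 60%/60% | 1 | 1.000 | 5.0% | 5.3% | 2.00 | 70.1% | 70.2% |
| 41.4%/58.6% | 2 | 0.971 | 4.7% | 4.2% | 1.96 | 73.2% | 74.3% |
| 50%/70% | 2.33 | 0.958 | 4.5% | 4.8% | 1.95 | 67.4% | 68.9% |
| 50%/80% | 4 | 0.901 | 3.9% | 3.9% | 1.88 | 60.1% | 63.3% |
| 40%/80% | 6 | 0.833 | 3.2% | 3.4% | 1.80 | 57.7% | 64.0% |

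Simulated and formula sizes differ a little because counts are discrete. CMH stays at 5.0% to 5.1% throughout. For a schedule odds ratio of 2, the normal approximation gives a power loss of 0.5 to 0.9 point over mean control rates of 10% to 70%. The simulated 1.1 points at 50% includes discreteness.

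**Site.** Site is also balanced. With a schedule odds ratio of 3 and a site standard deviation of 0.5 on the log-odds scale (again assumed), the loss against an analysis that accounts for both is 2.4 to 4.1 points. With a standard deviation of 1.0 it is 5 to 10 points. Stratifying by schedule alone recovers only part of this: in the extreme case at 50% toxicity, power is 56% crude, 59% by schedule and 66% by site.

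**The opposing effect.** Control patients are observed to month 3, about 13 weeks. Table 3 gives 51 weeks of pembrolizumab, so experimental patients are observed for up to 51 + 90/7 ≈ 64 weeks. Suppose the drug has no effect, the control rate to month 3 is p, and the hazard afterwards is a fraction f of the earlier hazard. The experimental rate is then 1 − (1 − p)^(1 + 51f/13). For f = 0.1 and p = 10%, 30%, 50% it is 13.6%, 39.1%, 61.9%, which gives odds ratios of 1.42, 1.50 and 1.62. The chi-square test rejects in about 14%, 32% and 46% of trials. With f = 0.05 the odds ratios are 1.21, 1.24 and 1.29. The value of f is an assumption; the direction follows from the footnote.

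**The case against.** A crude chi-square test with an odds ratio is conventional for toxicity tables, no alpha or power is attached to this comparison, and details are deferred to an analysis plan that is not shown. The size of any loss depends on rates that the article does not give. Cumulative doses are close (300 and 280 mg/m²), and selection of patients into schedules could offset a schedule difference as easily as enlarge it. Balance is only approximate, because minimization is stochastic and safety grouping follows treatment received. Rare Preferred Terms gain nothing from stratification, and a logistic model with every Cox factor could fail to converge on them. All of this stands and keeps the point minor. It does not remove the point, because the article itself names a test and an effect measure without strata, next to a model that uses them.

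A reader might infer more: that the harm comparison as a whole is conservative, that its odds ratio is biased towards 1, and that the plan therefore hides harm. The article does not support this. The gap between 2.0 and 1.80 to 1.96 is non-collapsibility: the crude and within-schedule odds ratios are two different quantities, each validly estimated. The unequal collection windows act in the opposite direction, plausibly more strongly.

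**Conclusion.** The point holds in a limited form. The toxicity comparison ignores a balancing factor that the efficacy model uses. If schedule predicts toxicity, the unstratified test is, other things equal, somewhat conservative. For 120 per arm, an even schedule split, near-exact balance and a within-schedule odds ratio of 2, the power loss runs from none (no schedule effect), through about 1 point or less (schedule odds ratio 2), to about 6 points (schedule odds ratio 6). The upper end needs a steep schedule effect for which the article offers no evidence. Strong site differences would add to the loss. The net direction of error in the harm comparison cannot be stated. This is a minor improvement, not a flaw that threatens the safety conclusion.

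**What to change.** In the analysis section or the statistical analysis plan, state that overall grade ≥3 toxicity, and only those adverse event terms with adequate counts, will be compared by a Cochran-Mantel-Haenszel test. Report a common odds ratio or risk difference, stratified by the cisplatin schedule entered at randomization. Keep the crude table as description, and keep simple or exact tests for rare Preferred Terms. Do not carry the full Cox factor set into a logistic model.

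The cost is a sentence or two and minor programming; schedule is already recorded at randomization. The unequal collection windows need separate handling, since stratification does nothing about them.

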## Methods

### Study design

ADRISK is a prospective, randomized, open-label, two-armed phase II multicenter superiority trial within the German Interdisciplinary Study Group of German Cancer Society (IAG-KHT). Patients with primary resectable stage III and IV (according to 7^th^ edition of TNM classification) HNSCC of the oral cavity, oropharynx, hypopharynx and larynx with pathologic high (R1, extracapsular nodal extension) or intermediate risk (R0 <5 mm; N≥2) after surgery who are eligible for cisplatin-based aRCT after surgery will receive either standard aRCT with cisplatin versus the same treatment + pembrolizumab (200 mg iv, in 3-week cycle, max. 12 months) (**Figure 1**). This clinical trial has been approved by the ethics committee of the University of Leipzig (076/18-ff).

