### Study objectives

The primary objective of ADRISK is to show that addition of pembrolizumab to aRCT with cisplatin improves EFS compared with aRCT alone in locally advanced intermediate and high-risk HNSCC after surgery. The primary endpoint EFS is defined as time from randomization to the first event, i.e.:

locoregional or distant recurrence (relapse),occurrence of further malignant disease (independent from localization and type),death from any cause, andinitiation of a new anti-cancer treatment without a previous event (primarily in case of safety concerns/toxicities observed which must be addressed in the patient**’**s treatment).

Secondary goals of the trial are to show that addition of pembrolizumab to aRCT with cisplatin improves OS compared with aRCT alone in locally advanced intermediate and high-risk HNSCC and to assess toxicity and show that addition of pembrolizumab to aRCT with cisplatin is safe in terms of toxicity (early *and* late toxicity). The duration of patients**’** observation is planned for at least 24 months post randomization, but preferably until LPLV (last patient**’**s last visit after 24 months of observation) to collect endpoint-events as comprehensive as possible.

Within the trial PD-L1 and p16 (only at tumor site oropharynx) expression in tumor tissue will be characterized by immunohistochemistry to explore the relationship between tumor PD-L1 and p16 expression and response to treatment with pembrolizumab. Therefore, material collected during the tumor resection will be analyzed locally at trial site and validated by reference pathologists in the central lab.

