#### Analysis population

The full analysis set (FAS, also called intention-to-treat (ITT) population) includes all randomized patients who start with the trial-related interventions. Randomized patients who withdraw their informed consent before the 1st trial intervention takes place will be excluded from the FAS.

The per-protocol (PPS) set is defined by all patients belonging to the ITT without major violations of the study protocol. Beside violations of eligibility criteria and patients not treated as randomized further protocol violations occurring during study conduct are reviewed and classified as major in the statistical analysis plan independently from arm allocation.

The safety population is defined by all randomized patients belonging to the FAS. In safety analyses, patients will be classified whether or not they received at least a single Pembrolizumab dose, irrespective of the randomized group allocation.

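### The Fisher test on serious adverse reactions (not the one on all serious adverse events) mixes how often events occur with how unblinded clinicians attribute them, and can reject when serious toxicity is equal

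*Protocol article*

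**What the plan says.** The relevant text is in the protocol article, under Statistical methods.

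- **Serious events, description.** Planned methods for analysis: "Serious adverse events will be reported descriptively (including a clinical causality assessment) by System Organ Class and Preferred Term according to MedDRA".
- **Serious events, test.** The same section continues that, where frequencies are relevant, for SAEs and "classified serious adverse reactions (by Preferred Term) exact Fisher test will be applied on SAE/SAR occurrences". One conditional sentence therefore plans two families of tests: SAEs whatever their cause, and SARs, the subset judged related.
- **Other safety tests.** That section also plans chi-square tests on adverse events by Preferred Term and on toxicities of grade 3 or higher, with odds ratios and 95% intervals. Neither depends on causality.
- **Groups compared.** Analysis population: in safety analyses, "patients will be classified whether or not they received at least a single Pembrolizumab dose, irrespective of the randomized group allocation".
- **Blinding and design.** Study design describes a "prospective, randomized, open-label, two-armed phase II multicenter superiority trial" in which both arms get the same adjuvant radiochemotherapy and one arm adds pembrolizumab.
- **Objective.** Study objectives include the secondary aim to "show that addition of pembrolizumab to aRCT with cisplatin is safe in terms of toxicity".
- **Collection window.** Footnote 4 to Table 4 (Schedule of trial procedures) has adverse events collected in the experimental arm until 90 days after treatment stops or a new anti-cancer treatment starts, but in the control arm only until the month-3 efficacy visit.

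The article does not say whether a SAR must be related to pembrolizumab or to any trial treatment, and it describes no blinded causality assessment.

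**The concern.** The safety question is whether adding pembrolizumab raises the risk of serious events, so the matching null hypothesis is equal risk in the two groups. The SAE test has that null. The SAR test has another: equal probability that an event occurs *and* is judged related. The two coincide only if the probability of being judged related is the same in both groups, and this design gives reason to doubt that.

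- If SAR means related to pembrolizumab, a patient who never received it cannot have one. The comparison count is zero by construction.
- If SAR means related to any trial treatment, the pembrolizumab group has one more drug to which an event can be attributed, and the assessor knows who received it. The same event may be called related more often there.

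A small SAR p-value could then be read as excess serious toxicity when part or all of it comes from labelling. The error would run against the experimental treatment and could conflict with the all-cause SAE test on the same data.

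**Working it through.** The document gives no figure for the safety tests to reproduce. Its 93-event calculation concerns EFS and does not enter here.

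**Inputs from the document.** 240 patients randomized 1:1 (Trial population), so about 120 per group; Fisher's exact test by Preferred Term; grouping by receipt of pembrolizumab; open-label assessment.

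**Assumptions, because the document gives no values.** Two-sided 5% level; true SAE risk *r* for a term, equal in both groups; fraction of SAEs judged related *f* with pembrolizumab and *g* without.

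**Method.** The SAR rate is *r·f* with pembrolizumab and *r·g* without. The rejection probability is the sum, over all pairs (a, b) with Fisher p ≤ 0.05, of Bin(a; 120, *r·f*) × Bin(b; 120, *r·g*). Setting *f* = *g* = 1 gives the all-cause SAE test. Example: *r* = 20%, *f* = 70%, *g* = 50% gives SAR rates of 14% and 10%.

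**Case 1: related to any trial treatment.**

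| Test, with true SAE risk equal | r = 5% | r = 10% | r = 20% | r = 30% |
|---|---|---|---|---|
| All-cause SAE | 2.1% | 2.8% | 3.4% | 3.6% |
| SAR, 50% vs 50% related | 1.1% | 2.1% | 2.8% | 3.2% |
| SAR, 60% vs 50% | 1.6% | 3.0% | 5.0% | 6.7% |
| SAR, 70% vs 50% | 2.5% | 5.3% | 11.3% | 17.7% |
| SAR, 80% vs 50% | 4.0% | 9.3% | 21.9% | 35.8% |

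With equal attribution the SAR test keeps its level. Inflation needs both unequal attribution and a fairly common term; at a 5% risk the rate stays below nominal in every row.

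**Case 2: related to pembrolizumab (*g* = 0).** The two-sided p-value for *x* versus 0 is 2·C(120, x)/C(240, x): 0.060 for *x* = 5 and 0.029 for *x* = 6. Six SARs are therefore enough, whatever happened in the comparison group. With half of the events judged related, rejection is 8.1%, 56%, 98% and about 100% at SAE risks of 5%, 10%, 20% and 30%.

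**Is the all-cause SAE test like-for-like?** Only over a common window. If Table 4's footnote 4 also governs SAEs, the experimental arm is observed for about 51 weeks + 90 days = 357 + 90 = 447 days, roughly 15 months, against 3 months in control. With equal constant hazards and a three-month risk *q*, the 15-month risk is 1 − (1 − *q*)^5: 9.6%, 14.1% and 22.6% for *q* = 2%, 3% and 5%. Fisher's test on these pairs rejects in 64%, 85% and 98% of trials. Removing the SAR test without aligning the window would leave a comparison that can also reject under equal toxicity.

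**The case against.** The strongest reply is that little depends on the SAR p-value. Serious events are primarily described; Fisher's test is added only at relevant frequencies; the all-cause SAE test is in the same sentence; chi-square tests cover all adverse events and the higher-grade toxicities. No confirmatory claim rests on SARs. This stands, and it is why the point is minor.

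Second, the tests are per Preferred Term, and serious-event risks of 20% to 30% for one term are assumed. This also stands: for rare terms in Case 1 there is no inflation. The condition of relevant frequencies does, however, direct the test to the commoner terms, where the fault is larger.

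Third, the largest figures need the pembrolizumab-only definition, which the article does not state. Radiotherapy and cisplatin are listed among the trial interventions, which fits the broader meaning. The definition may be in the full protocol or the SAP, neither of which is shown, so its absence is no criticism. But neither definition alone removes the problem: one makes the comparison count zero, and the other leaves unblinded attribution with an extra candidate drug.

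A reader might infer that all the planned Fisher tests measure attribution instead of frequency. The document does not support that: the SAE test ignores causality, and even the SAR test reflects occurrence multiplied by attribution and keeps its level when attribution is equal.

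**Conclusion.** The concern holds for the SAR half of the Fisher testing only. That comparison mixes occurrence with unblinded attribution to a drug that one group receives, and it can reject when serious toxicity is equal. Under Case 1 with 70% versus 50% called related, the false rejection rate runs from 2.5% at a 5% SAE risk to 17.7% at 30%. Under Case 2 the test is not a comparison of toxicity at all. These sizes rest on assumed SAE risks and attribution fractions, 120 patients per group and a two-sided 5% level. That attribution will in fact differ is a risk of the design, not something the document shows.

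It would go too far to conclude that the trial's comparative safety analysis is invalid, or that the article adopts the pembrolizumab-only meaning. Nor should the all-cause SAE test be taken as sound as it stands: it is free of the attribution fault, but is like-for-like only over a common collection window. Severity is minor.

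**What to change.** In Planned methods for analysis, or in the SAP, which the article says will be finalized before database closure, replace the Fisher sentence with wording such as: *Where SAE frequencies by Preferred Term are relevant, Fisher's exact test will be applied to SAE occurrences regardless of causality, counted over a collection window common to both groups (for example, to month 3 after randomization). SARs, and SAEs after that window, will be tabulated descriptively by group and not tested between groups.*

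Month 3 is only an example; it follows from the control-arm limit in footnote 4 to Table 4. The change takes one or two sentences and needs no new data or patients. The costs are that related events have no p-value, background events dilute a drug-specific signal in the all-cause test, and later events, including late immune-related ones, are reported only descriptively. The SAR and late-SAE tables keep that information visible.
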